## Period of observation for (S)AE

The period of observation for collection of adverse events extends from the time of patient recruitment to the study until 30 days following the end of the last treatment cycle.

If the investigator detects a (serious) adverse event in a study patient after the end of the observation period, and considers the event possibly related to prior study treatment, he or she should contact the study coordinator to determine how the adverse event should be documented and reported.

Patients who require an interruption in dosing of > 2 weeks (due to a
erlotinib related adverse event not manageable with optimal supportive medication) will discontinue erlotinib treatment and be taken off study. Erlotinib re-challenge after interruption of dosing will occur only if the investigator considers it is in the best interest of the patient to re-challenge.

## Supportive care measures

### Diarrhea

Diarrhoea has been commonly observed (~ 50%) and is usually transient in nature. Previous trials have shown that the frequency and severity of diarrhoea rarely hindered administration of erlotinib and could be managed with loperamide. The recommended dose is loperamide 4 mg at first onset, followed by 2 mg q 2 – 4 hours until diarrhoea free for 12 hours.

### Rash

Skin rash or dermatosis (Grade 1 – 2) has been observed during the first several days of treatment with erlotinib in more than 50% and has been observed to diminish in severity despite continued treatment in many patients. In some patients, particularly when a superimposed infection is suspected, this rash appeared to improve with topical and oral antibiotics. Anecdotal reports of improvement have occurred with several agents. In patients with severe rash, treatment may need to be discontinued or the dose reduced (see table 11 above).

See Appendix 5 for additional guidelines on the treatment of rash.

## Criteria for Premature Withdrawal

The local investigator and the principle investigator have the right to withdraw subjects from the study in the event of intervening illness, adverse events or treatment failure after a prescribed procedure, protocol violations, cure, administrative reasons or other reasons.

If the reason for removal of a subject from the study is an adverse event or an abnormal laboratory test result, the principal specific event or test will be recorded on the Case Report Form.

## Pre-treatment & treatment evaluations formalities

The participating investigator in charge of the patient is responsible for verifying that the patient is eligible before inclusion in the study. If any of the inclusion criteria are not met and any of the exclusion criteria are present, the patient must not be enrolled. Once a patient is enrolled in the program, he/she will only be identified by his/her initials and the assigned patient number.

Page one and two of the CRF will be considered as the Inclusion Form, documenting the patient’s fulfilment of the eligibility criteria and the completion of the written informed consent. These CRF pages have to be completed by the investigator and faxed to the central data management office at **[name].**

All sites as well as the central data office will maintain a patient log for all included patients.

### Schedule of Assessments

Table 4.

|  | **Screening/**  **Baseline**  **Maximum days prior to first treatment** | **Treatment Period**  **Timing** | **End of Study** |
| --- | --- | --- | --- |
| Informed Consent | 3 weeks | - | - |
| Demographics | 3 weeks | - | - |
| Medical history | 3 weeks | - | - |
| Physical examination | 3 weeks | Every 6 weeks | X |
| Pregnancy test1 | 48 hours before starting erlotinib | - | - |
| Laboratory2 | 2 weeks | Every 6 weeks | X |
| Tumor measurements3 | 2 weeks | - On day 14.  - Then every 6 weeks from treatment initiation, up to 6 months of follow-up  - Thereafter q 12 weeks | X |
| Tumor Biopsy and mutation analysis 4 | pretreatment |  |  |
| ECOG Performance Status | 7 days | Every 6 weeks | X |
| erlotinib administration |  | Continuously | - |
| Safety5 | - | Recorded throughout study | X |
| Survival | - | - | X |

1. In women of childbearing potential only
2. Hematology: Hemoglobin, WBC, granulocytes and platelet count, INR (Only for patients receiving warfarin or coumadin-derivative. To be done twice per week during for 3 weeks; then weekly or more often as clinically indicated.) Biochemistry: Alkaline phosphatase, Serum bilirubin, Serum creatinine, AST (SGOT) and ALT (SGPT). Only laboratory abnormalities linked to unexpected clinical symptoms will be documented in the CRF.
3. CT scans, MRI or X-ray as per Institutional Standards and FDG-scan (appendix 5 for CT-scan and FDG-scan specification). The first FDG scan is at day 14. It is also proposed that a CT-scan is performed at the same time point.
   For responding patients, a confirmatory evaluation should be repeated at least 4 weeks (normally at the next 6 week interval evaluation) after the initial determination of response.
4. A formaline fixed paraffin tissue block representative of the patient's primary cancer at the initial diagnosis or a pretreatment bronchoscopy biopsy or a biopsy from a metastatic site will be sent to the Laboratory of Molecular Oncology, Oncology Centre, AZ-VUB.
5. Serious Adverse Events, Adverse Events leading to premature withdrawal, unexpected erlotinib related AEs and erlotinib related rash.

### Study Assessments Recording Formalities

#### Clinical Assessments

All patients will provide written informed consent. The following will be completed according to the schedule of assessments (table 4):

- Demographics including smoking status (Never smokers with a lifetime exposure of fewer than 100 cigarettes, versus Former Smokers (with a maximum of 15 pack years): number of pack years.
- ECOG Performance Status
- Tumor measurement (CT, MRI or X-Ray AND FDG) with assessment of tumor done according to RECIST. For responding patients, a confirmatory evaluation should be repeated at least 4 weeks after the initial determination of response.
- Safety: Serious Adverse Events (SAEs, Adverse Events leading to premature withdrawal, unexpected erlotinib related AEs and erlotinib related rash)

#### Laboratory Assessments

The following will be completed according to the schedule of assessments

- For all females of childbearing potential a negative pregnancy test (urine or serum) must be obtained locally within 48 hours before starting therapy.
- Hematology
- Hemoglobin
- WBC, granulocytes and platelet count
- INR (Only for patients receiving warfarin or coumadin-derivative. To be done twice per week during 3 weeks; then weekly or more often as clinically indicated.)
- Biochemistry
- Serum bilirubin
- Serum creatinine
- Alkaline phosphatase
- AST (SGOT)
- ALT (SGPT)

#### Biopsy Collection

A formalin fixed paraffin tissue block representative of the patient's primary cancer or a metastatic site will be send to prof. dr. [name], EXPA FIELT AZ-VUB, [name], together with the "Request for EGFR mutation analysis form" and "Screening Eligibility Form".

The methodology for tissue sampling is further elaborated in chapter 15. Several alternative phone numbers are provided:

**[contact] ([name]) or [name] ([name]) or [name] ([name]) or [name] ([name]) or [name] ([name]) or [name] ([name])**

# Tumor response evaluation formalities

Clinical tumor response will be evaluated according to the Response Evaluation Criteria in Solid Tumors (RECIST) guidelines (appendix 2). An electronic version of the reference publication on RECIST methodology will be provided on CD-ROM. For matters of discussion, the FAQ-web page concerning RECIST methodology at the EORTC website will be consulted ([www.eortc.be](http://www.eortc.be/)). The details of the response assessment are described in section 9.

FDG-PET and CT of disease sites (as well as other imaging exams needed to evaluate local or metastatic disease) will be used to evaluate disease status at base line, 2 weeks (FDG-PET obligatory, CT-scan optional) and weeks 6 and 12 post treatment initiation.

Then first 6 months post-treatment initiation, CT-scans will be performed every 6 weeks. Subsequent re-evaluations will be performed at least every 12 weeks until disease progression in accordance with current clinical management.

Response Rate, Metabolic Response Rate, Response: definitions in section 9.

# Patient study withdrawal formalities

Patients that participate in this study may be withdrawn from the study for the following reasons (different from disease progression or unacceptable toxicity):

- At their own request or at the request of their legally authorized representative.
- In case the investigator considers that continuation of study treatment is detrimental to the patients’ well being.
- At the specific request of the sponsor

In all cases, the reason for and date of withdrawal must be recorded in the case report form and in the patients’ medical records. The patient must be followed up to establish whether the reason was an adverse event, and, if so, this must be reported in accordance to the procedures related to (S)AE reporting.

The decision of a patient to withdrawal from the study for whatever reason will have no influence on the attitude of the investigator, the members of his team or the nursing group. The patient will continue to receive best treatment as estimated by the investigator.

# Statistical considerations

The purpose of this study is to obtain an estimate of the proportion of patients experiencing a progression free survival (PFS) at three months in order to position this type of first-line therapy for further study in comparison to the results that can be obtained with current first-line chemotherapy in advanced non-small cell lung cancer.

The premises for the sample size determination are as follows:

With current chemotherapy, progression free survival of 60% or less is obtained at 3 months follow-up3.

Taking into account the general better tolerability of RTKI’s it is proposed that if a PFS of > 70% can be obtained, that this treatment definitely deserves further evaluation against chemotherapy in the first-line treatment of advanced non-small cell lung cancer.

If the study results in a PFS less than 50 % at three months, single agent RTKI’s should not be further evaluated in this setting as outcomes inferior in terms of efficacy to the current standard are not acceptable.

Based on these premises, a one step Fleming design requires at least 33 patients to be included in the study (

With the provision of a margin for eligibility/evaluation issues, the prospective number of patients to be included will be 40 patients.

When, alternatively, statistics normally used for phase II design based on response, are applied to the PFS outcome proportions (freedom from progression regarded as a clinical benefit response), then, in a Simon minimax two-stage design and with α = 5%, β = 20%, for rejecting the null hypothesis (p0) of a freedom from progression rate < 60%, in a first stage, more than 8/13 patients should have a progression free survival of > 3 months. The second stage would lead to an accrual of 35 evaluable patients of whom at least 26 should be free from progression at 3 months to establish a probable freedom from progression rate of > 80% at 3 months. Again, with the provision of a margin for eligibility/evaluation issues, the prospective number of patients to be included will be 40 patients.

With an estimated maximal 10% mutation rate in the overall population of NSCLC, this cohort of patients could result from a baseline population of at least 400 patients with advanced non-small cell lung cancer.

Survival (time to progression and overall survival) will be calculated from the start of therapy until disease progression or death or last follow-up according to the Kaplan-Meier method with SPSS statistical software (release 7.5, 1996; SPSS Inc, Chicago, IL).

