| **Statistical considerations**  **Design**: phase II  **Nr of patients**: based on results obtained with chemotherapy a progression free survival of >= 60% could be expected at 3 months. The treatment will be considered for further development if a PFS > 70% can be obtained at 3 months. The treatment will be considered inappropriate as a first line if PFS < 50% at 3 months. Therefore a maximum of 40 patients will be included plus the number needed to replace patients that will drop out for reasons other than disease progression and patients not meeting eligibility criteria. |

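### The go criterion of an obtained 3-month PFS above 70% is not tied to a critical count: read as an observed rate, it passes a regimen with a true rate of 70% only about half the time, and it conflicts with the Simon rule in the same section.

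*Protocol*

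**What the plan says.** The protocol's Statistical considerations set out three rates as premises for the sample size. The benchmark is "With current chemotherapy, progression free survival of 60% or less is obtained at 3 months". The upper limit is that "if a PFS of > 70% can be obtained, that this treatment definitely deserves further evaluation". The lower limit begins "If the study results in a PFS less than 50 % at three months", and below it single-agent treatment is not to be pursued in this setting.

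From these premises the section says that "a one step Fleming design requires at least 33 patients to be included in the study". The text then breaks off at an opening parenthesis. With a margin for eligibility and evaluation problems, "the prospective number of patients to be included will be 40 patients".

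The section then offers an alternative, a Simon minimax two-stage design "with α = 5%, β = 20%, for rejecting the null hypothesis (p0) of a freedom from progression rate < 60" percent. More than 8 of 13 patients must be progression-free at the first stage. The second stage needs "35 evaluable patients of whom at least 26 should be free from progression at 3 months", which is meant to establish a probable rate above 80%.

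The synopsis gives the go criterion again, as a development decision: "The treatment will be considered for further development if a PFS > 70% can be obtained at 3 months". It calls the treatment inappropriate below 50%. It mentions neither the Fleming nor the Simon design.

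**The concern.** A one-stage test of a null rate against an alternative declares success at a count lying between the two rates. If the alternative itself becomes the hurdle for the observed rate, a treatment that truly has that rate will clear it only about half the time, because the observed proportion falls roughly evenly on either side of the truth. The power behind the sample size then no longer describes the decision that will be taken.

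The protocol appears to do this with 70%: it is a premise for the sample size and also the figure the result must exceed. A count-based rule from a different pair of rates stands beside it, and neither is named as governing. At stake is the trial's main conclusion, since a reader could not say in advance which results lead to further development or how often a worthwhile regimen would be passed.

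**Working it through.** **Inputs.** From the Statistical considerations: rates of 50%, 60% and 70%; Fleming minimum 33; planned number 40; Simon rule of more than 8/13, then at least 26/35, with alpha 5% and beta 20%. *Assumed:* one-sided testing, and the 5% level carried over to the Fleming design.

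**1. The plan's own figures.** Fleming, normal approximation: n = [(z(1−alpha)·√(p0·q0) + z(power)·√(p1·q1)) / (p1 − p0)]².

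- 50% vs 70%, 5%, 80% power: [(1.645×0.5 + 0.842×0.458)/0.2]² = 36.5, so 37.
- 50% vs 70%, 5%, 75% power: [(1.645×0.5 + 0.674×0.458)/0.2]² = 32.01, so 33.
- 60% vs 70%, 5%, 80% power: 142.
- 60% vs 80%, 5%, 80% power: [(1.645×0.490 + 0.842×0.4)/0.2]² = 32.6, so 33.

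Among pairs of the three listed premises, only 50% vs 70% gives a number in the thirties, and 33 then corresponds to about 75% power. The Simon inputs (60% vs 80%) also give 33, so the Fleming pair cannot be identified with certainty.

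The Simon design reproduces. Its probability of success is Σ over x = 9 to 13 of P(X1 = x | 13, p) × P(X2 ≥ 26 − x | 22, p), which is 0.0499 at p = 0.60 and 0.808 at p = 0.80.

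**2. The go rule read as an observed rate above 70%.** The smallest count r with r/n > 0.70 is found, then P(X ≥ r | n, 0.70). Beside it stands the smallest count giving one-sided alpha of at most 5% against 50%.

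| Evaluable n | Count for > 70% | P(go) at true 70% | Count, 50% vs 70% | P(go) at true 70% |
|---|---|---|---|---|
| 33 | 24 | 45.0% | 22 | 73.3% |
| 34 | 24 | 55.5% | 23 | 69.3% |
| 35 | 25 | 51.0% | 23 | 77.3% |
| 36 | 26 | 46.6% | 24 | 73.7% |
| 37 | 26 | 56.6% | 24 | 80.7% |
| 38 | 27 | 52.4% | 25 | 77.5% |
| 39 | 28 | 48.2% | 26 | 74.0% |
| 40 | 29 | 44.1% | 26 | 80.7% |

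The observed-rate rule is lower at every n. The loss is 73.3 − 45.0 = 28 points at 33 and 80.7 − 44.1 = 37 points at 40. In return it is stricter: at a true 50% its go probability is 0.7% (n = 33) and 0.3% (n = 40), against 4.0% for the critical count at both sizes.

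**3. The two rules in the same section.** 25/35 = 71.4% exceeds 70% but is one short of the Simon requirement; 26/35 = 74.3%. At a true rate of 70% the full Simon rule succeeds with probability 32.7%, against 51.0% for an observed rate above 70% at n = 35.

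**The case against.** There is a fair case against this.

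- **True rate, not observed rate.** The 70% sentence stands under the premises for sample size, where a target true rate belongs, and it may state a sufficient condition only. This has some force, but the synopsis uses the same figure as the development decision and the paired 50% limit is a limit on the study result. If 70% is a true rate, the only legible success count left is Simon's, which rests on 60% vs 80% and passes a true 70% a third of the time. The wording needs settling on either reading.
- **50% vs 70% is inferred.** This stands. If the Fleming design is 60% vs 80% at 5%/20%, the 5% cut-off at n = 33 is 25/33 = 75.8% (alpha 4.4%), and an observed rate above 70% is then more lenient than the test. A reader might take 70% as plainly the Fleming alternative; the protocol does not label it so.
- **A cut-off may have stood in the text.** The Fleming parenthesis is not legible and could have held error rates or a critical value. Its absence is no defect.
- **Less than half.** A reader might infer that a true 70% always fails more often than it passes. That holds at 33, 36, 39 and 40 evaluable patients, but not at 34, 35, 37 or 38.
- **The zone from 50% to 70%.** The section's stated purpose is estimation, and an inconclusive band around a 60% benchmark is a legitimate choice.

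**Conclusion.** The point holds in a limited form. As written, the go criterion is not linked to a legible critical value. Read as an observed-rate rule, it gives a regimen with a true 3-month rate of 70% a go with probability 44% to 57% over 33 to 40 evaluable patients, against 69% to 81% for a critical count testing 50% against 70%. The first range depends only on the observed-rate reading and on treating 3-month PFS as a binary outcome without censoring. The comparison also depends on the assumed pair of rates and one-sided 5% level.

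The conflict with the Simon rule needs no assumed error rates: 25 of 35 passes one criterion and fails the other, and the section does not say which governs.

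The documents do not support the stronger inference that the sample size is wrong or that the success threshold must be lowered. This is a single-arm phase II trial whose result informs whether to study further. A wording correction is warranted, at less than the highest severity.

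**What to change.** In the synopsis and the Statistical considerations, name one governing design with its null rate, alternative, alpha and power. Replace the phrase about a PFS above 70% being obtained with that design's critical count for the evaluable number. Mark the other design as supporting only, or remove it.

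- If 50% vs 70% is meant, an example is at least 26 of 40 progression-free at 3 months: alpha 4.0%, power 81% at a true 70%. The downside is a 32% go probability when the true rate only equals the 60% benchmark.
- If 60% vs 80% is meant, the existing Simon count can stand, with its 33% success probability at a true 70% disclosed and the 70% criterion withdrawn.
- If an observed rate above 70% is kept, state what it delivers at n = 40 (at least 29): go probability 7% at a true 60%, 44% at 70%, 72% at 75% and 91% at 80%.

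A sentence on how a result between 50% and 70% will be read would help, but is optional. The cost is wording in two places and no extra patients. The choice between the options is the sponsor's, because it trades missing a true 70% regimen against advancing one no better than chemotherapy.

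### Section 15 sets out two decision schemes for 3-month PFS without saying which governs, and they can disagree on the same data

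*Protocol*

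**What the plan says.** Two schemes stand in section 15 (Statistical considerations).

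**Scheme A.** Go: "if a PFS of > 70% can be obtained, that this treatment definitely deserves further evaluation against chemotherapy". Drop: "If the study results in a PFS less than 50 % at three months", in which case the drug class should not be pursued in this setting. From these premises the section derives a one-step Fleming design of at least 33 patients, raised to 40 for eligibility and evaluation losses. The synopsis states the same pair: "The treatment will be considered for further development if a PFS > 70% can be obtained at 3 months" and "The treatment will be considered inappropriate as a first line if PFS < 50% at 3 months". It mentions no stages and no early look.

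**Scheme B.** Introduced as an alternative, this is a Simon minimax two-stage design with α = 5%, β = 20%, null 60% and target 80%. Its hurdles are "in a first stage, more than 8/13 patients should have a progression free survival of > 3 months" and then "35 evaluable patients of whom at least 26 should be free from progression at 3 months". It too ends at 40 patients.

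The chemotherapy benchmark behind both is worded in opposite directions. Section 15 has "With current chemotherapy, progression free survival of 60% or less is obtained at 3 months"; the synopsis has "a progression free survival of >= 60% could be expected at 3 months".

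**The concern.** A single-arm phase II trial whose purpose is a go/no-go judgement needs one rule fixed in advance. Here the schemes differ in the go criterion (above 70% observed, against at least 26/35, which is 74.3%), in the rate they are built around, and in whether the trial can stop after 13 patients. If neither is declared to govern, the choice can be made after the data are known. Whether enrolment depends on an early look is a matter of conduct, and a protocol should settle it.

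The benchmark wording matters because 60% is the null value of scheme B. Read as an upper bound for chemotherapy, it is a sensible figure to beat. Read as a lower bound, rejecting 60% would not show that chemotherapy had been matched.

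**Working it through.** **Inputs**, all from section 15:
- A: go if the 3-month rate is above 70%, drop if below 50%.
- B: null 60%, target 80%, α 5%, β 20%; continue if at least 9 of 13; succeed if at least 26 of 35.

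Assumptions: 3-month status is known for every evaluable patient, so the rate is a simple proportion. Scheme A is read literally as an observed proportion and applied to 35 patients, so that both schemes face the same data.

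**Step 1. Reproduce the plan's own figure.** With X1 ~ Bin(13, p) and X2 ~ Bin(22, p):

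P(go under B) = Σ over x1 = 9 to 13 of P(X1 = x1) × P(X2 ≥ 26 − x1)

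This gives 0.0499 at p = 0.60 and 0.808 at p = 0.80. A search over designs from n = 28 upward finds none smaller than 35 that meets both error limits. The Simon figures are correct as stated.

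**Step 2. Put A on the same scale.** Above 70% of 35 means x > 24.5, so go needs x ≥ 25, and P(go under A) = P(Bin(35, p) ≥ 25). Drop needs x ≤ 17 (17/35 = 48.6%). Counts of 18 to 24 receive no verdict under A.

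**Step 3. Find data on which they part.**
- 25/35 = 71.4%: go under A; one short of 26 under B, so 60% is not rejected.
- 8/13 = 61.5%: B stops the trial. A has no look, and 61.5% lies between its two thresholds.

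**Step 4. Probabilities.** Any go under B is also a go under A if all 35 are observed, so disagreement is the difference between the two go probabilities.

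| True rate | B stops at 13 | B go | A go (n = 35) | Disagree |
|---|---|---|---|---|
| 60% | 64.7% | 5.0% | 11.2% | 6.2% |
| 70% | 34.6% | 32.7% | 51.0% | 18.3% |
| 80% | 9.9% | 80.8% | 92.5% | 11.7% |

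At a true 70%, the single count 25/35 has probability C(35,25) × 0.7^25 × 0.3^10 = 14.5%. The remaining 18.3 − 14.5 = 3.8 points are trials that B would have stopped at 13 but that would have ended with 26 or more.

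**Step 5. Sensitivity to the denominator of A.** At n = 33, go needs at least 24 (72.7%): 45.0% at a true 70% and 9.2% at 60%. At n = 40 it needs at least 29 (72.5%): 44.1% and 7.1%.

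**The case against.** The best defence is that the text does give a ranking, if only implicitly. The synopsis states scheme A alone. In section 15 the one-step design comes first and already yields 40. The Simon paragraph is conditional in tone and arrives at the same 40, so it can be read as a cross-check of the sample size. Section 11.3 (Study Duration) has recruitment run until the planned number is reached, with no hold at 13, and section 15 describes its purpose as estimation.

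Much of this stands. It makes the ambiguity smaller than two equal live designs would. It does not remove it: the Simon paragraph states hurdles that patients should meet at both stages, with α and β, and nothing calls it supportive.

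Four stronger readings are tempting and are not supported:
- **Scheme A is a 5% test of 50%.** That would give a cut-off of 22/33, with go probabilities of 73% at a true 70% and 28% at a true 60%. No such cut-off is in the protocol, and 22/33 = 66.7% does not satisfy the stated above-70% criterion. Under that criterion a drug at the 60% benchmark passes in 11% of trials at n = 35, which is not often.
- **The Fleming size of 33 is wrong.** The bracket after it is cut off in the available text, so its null, target, α and power cannot be read, and 33 cannot be faulted.
- **The verdicts are outright opposites.** Failing B means that 60% was not rejected. A's drop verdict applies only below 50%, which 25/35 does not approach.
- **Simon should govern because its figures reproduce.** That would penalise the other design for text that cannot be read.

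**Conclusion.** The point holds. Section 15 contains two decision schemes for the trial's main question, does not rank them, and leaves open whether a look at 13 patients takes place. At a common n of 35 the conflict at the final analysis is one count, 25/35. To this are added the stage-1 stops, which occur in 35% of trials at a true rate of 70%. Overall the schemes disagree in about 18% of trials at a true 70% and about 6% at a true 60%.

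These sizes rest on reading the above-70% rule as an observed proportion among 35 evaluable patients; no test cut-off is assumed for scheme A. The opposite direction of the chemotherapy benchmark in the synopsis and section 15 is a lesser, separate inconsistency that should be settled at the same time.

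**What to change.** In section 15 and the synopsis:
1. Name one governing design, with its null, target, α, power and a numerical cut-off.
2. State whether the look at 13 evaluable patients applies. If it does, say how accrual is handled while their 3-month status is awaited.
3. Label the other design as a supportive check of N = 40, or delete it.
4. Give the chemotherapy benchmark in one direction in both places.

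The choice of design is the sponsor's. If 60%/80% is chosen, the stated Simon rule can stand as written (α 0.0499, power 0.808). A single-stage rule of at least 27/36 (α 0.045, power 0.832) also fits within 40. If 50% and 70% are chosen as null and target, then at one-sided 5% and 80% power (assumed here) an exact single-stage rule is at least 24/37 (α 0.049, power 0.807). That also fits within 40, but 24/37 = 64.9%, so the above-70% wording would have to be revised to match.

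Cost: an amendment to protocol wording, plus a possible short accrual hold at 13 patients if the two-stage design is kept. No extra patients.

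### The Fleming minimum of 33 does not match the 50%/70% premises at the only error rates legible in the section; these give 37

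*Protocol*

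**What the plan says.** Section 15 (Statistical considerations) sizes the trial on the proportion of patients progression-free at three months. It lists three premises:

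- chemotherapy benchmark: "With current chemotherapy, progression free survival of 60% or less is obtained at 3 months follow-up"
- go: "if a PFS of > 70% can be obtained, that this treatment definitely deserves further evaluation against chemotherapy"
- stop: "If the study results in a PFS less than 50 % at three months, single agent RTKI’s should not be further evaluated"

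It then concludes: "Based on these premises, a one step Fleming design requires at least 33 patients to be included in the study". An opening bracket follows and the text at hand stops there. A margin for eligibility and evaluation problems takes the planned inclusion to 40.

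The next paragraph gives a second justification, "in a Simon minimax two-stage design and with α = 5%, β = 20"%, with a null rate of 60% and a target rate of 80%. It leads to 35 evaluable patients and again to 40 included.

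The synopsis (section 3) repeats the 70% go threshold and the stop rule ("The treatment will be considered inappropriate as a first line if PFS < 50% at 3 months"). It caps inclusion at 40 plus replacements for ineligible patients and for drop-outs other than progression.

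**The concern.** The number 33 is presented as a consequence of the premises just listed. The natural test in those premises is 50% (stop) against 70% (go). At the error rates that the section does state, 33 is too small for that test. It is, however, the size that the same formula gives for 60% against 80%, and 80% is not among the premises.

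What is at stake is which null hypothesis the trial can reject, and with what power. The two readings lead to different decisions on the same data. With 33 evaluable patients:

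- Under 60%/80%, success needs 25/33 (75.8%). A result of 24/33 (72.7%) would exceed the 70% go threshold and still fail the test.
- Under 50%/70% at alpha 5%, success needs 22/33 (66.7%). That rejects 50% but lies below the go threshold.

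A reader who takes 33 as adequate for 50% against 70% at 5%/20% would credit the design with a property it lacks.

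**Working it through.** **Inputs.** p0 = 50% and p1 = 70% come from the stop and go premises in section 15. The pair 60%/80% comes from the Simon paragraph of the same section. Alpha 5% and beta 20% are stated for Simon only; using them for Fleming, with alpha one-sided, is an assumption. The stated Fleming size is 33.

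**Formula (Fleming, single stage).** n = [(z_alpha·√(p0·q0) + z_beta·√(p1·q1)) / (p1 − p0)]², with q = 1 − p, rounded up.

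**1. Trying to reproduce 33 from the premises at 5%/20%** (z = 1.645 and 0.842):

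- 50%/70%: [(1.645 × 0.5 + 0.842 × 0.458) / 0.2]² = 36.49, so 37.
- 60%/70%, the other pair that the premises could suggest: 141.96, so 142.

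Neither gives 33.

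**2. The Simon pair at 5%/20%.** 60%/80%: [(1.645 × 0.490 + 0.842 × 0.4) / 0.2]² = 32.63, so 33.

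**3. Sensitivity to the unreadable error rates** (formula, rounded up):

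| alpha (one-sided) / beta | 50%/70% | 60%/80% |
|---|---|---|
| 5% / 20% | 37 | 33 |
| 5% / 10% | 50 | 44 |
| 10% / 20% | 27 | 24 |
| 10% / 10% | 38 | 33 |
| 5% / 25% | 33 (32.01) | 29 |
| 10% / 15% | 32 (31.12) | 28 |

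The first four rows are the usual pairs. None gives 33 at 50%/70%; two do at 60%/80%. At 50%/70%, 33 needs alpha 5% with 75% power, and 10%/15% comes within one patient.

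**4. Exact binomial properties:**

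| Pair | Success rule | alpha | power |
|---|---|---|---|
| 50%/70% | ≥ 22/33 | 4.0% | 73.3% |
| 50%/70% | ≥ 21/33 | 8.1% | 83.9% |
| 50%/70% | ≥ 24/37 | 4.9% | 80.7% |
| 50%/70% | ≥ 26/40 | 4.0% | 80.7% |
| 60%/80% | ≥ 25/33 | 4.4% | 80.0% (0.79996) |

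For 50%/70%, 37 is also the first size at which an exact rule holds 5% and reaches 80% power. For 60%/80%, 33 falls short of 80% by a trivial amount, and the first size strictly above it is 36 (≥ 27: alpha 4.5%, power 83.2%). The agreement of 33 with 60%/80% is therefore agreement with the formula, met to rounding by the exact calculation.

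**5. The Simon figures.** More than 8/13 at stage one and at least 26/35 overall give alpha 0.0499 at 60% and power 0.808 at 80%. That paragraph reproduces; the mismatch is confined to the Fleming sentence.

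**The case against.** The strongest objection is that the deciding inputs are out of sight. The bracket directly after 33 may well have held the Fleming error rates, and text lost in reading the file is not an error in the plan. The Simon paragraph is introduced as an alternative, and nothing says that its 5%/20% applies to Fleming. Other rates could rescue the number: 5% with 75% power gives 33 at 50%/70%, and if alpha up to 10% was accepted, a cut-off of 21/33 has 84% power. This stands, and it makes the point conditional.

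A reader might infer that 33 is simply wrong for 50%/70%, or that it was computed for 60%/80%. The document supports neither as fact. The first depends on error rates that cannot be read. The second is a back-calculation: 60%/80% gives 33 at 5%/20% and also at 10%/10%, so even under that reading the error rates are not identified. Nor does it follow that the sponsor should adopt 60%/80%. That would replace the 50% and 70% thresholds stated in both section 15 and the synopsis.

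It is also fair to say that the practical effect is limited, because 40 patients are planned and 26/40 gives 80.7% power at 50%/70%. This stands in part. Section 15 counts the evaluability margin inside the 40, so the full 40 evaluable are assured only if the synopsis rule on replacements is applied.

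**Conclusion.** The point holds in conditional form. At one-sided alpha 5% and 80% power, the only error rates legible in the section, the stated 50%/70% premises need 37 evaluable patients, four more than the 33 given. No usual alpha/beta pair yields 33 from those premises. If alpha is 5%, 33 evaluable patients leave a false-negative risk of about 27% at a true rate of 70%, against 20% at the stated beta.

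The conclusion rests on borrowing the Simon error rates and on reading the stop and go thresholds as p0 and p1. A different alpha in the missing bracket would change the power figure, and a target of about 75% power would remove the discrepancy. It is a mismatch worth correcting, but it does not threaten the planned enrolment.

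**What to change.** First check the error rates in the bracket of the source protocol against the figures above. Then state, in section 15 and the synopsis, one p0/p1 pair with alpha, power and success cut-off that agrees with the sample size and with the go/no-go thresholds. The options are:

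- **50%/70% at 5%/20%:** restate the minimum as 37 evaluable within the planned 40, success if at least 24/37 (alpha 4.9%, power 80.7%); if all 40 are evaluable, at least 26/40 (alpha 4.0%, power 80.7%). Fix the cut-off for each possible evaluable number, because exact power at alpha 5% dips to 77.4% at 38 (≥ 25) and 74.0% at 39 (≥ 26).
- **50%/70% with 33 kept:** state success if at least 22/33, alpha 4.0%, power 73%.
- **60%/80%, if that is what was meant:** state at least 25/33 (alpha 4.4%, power 80.0%) and explain how this rule fits with the 50% and 70% thresholds. This changes the decision criteria and should be made openly as such.

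The first two options cost a sentence or two in section 15 and a matching synopsis line; the third also needs the thresholds reworked. None needs enrolment beyond 40.
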